## Abstract

**Background:**

Current population surveys suggest around 20% of Australians meet diagnostic criteria for an alcohol use disorder. However, only a minority seek professional help due to individual and structural barriers, such as low health literacy, stigma, geography, service operating hours and wait lists. Telephone-delivered interventions are readily accessible and ideally placed to overcome these barriers. We will conduct a randomised controlled trial (RCT) to examine the efficacy of a standalone, structured telephone-delivered intervention to reduce alcohol consumption, problem severity and related psychological distress among individuals with problem alcohol use.

**Methods/design:**

This is a single site, parallel group, two-arm superiority RCT. We will recruit 344 participants from across Australia with problem alcohol use. After completing a baseline assessment, participants will be randomly allocated to receive either the Ready2Change (R2C) intervention (*n* = 172, four to six sessions of structured telephone-delivered intervention, R2C self-help resource, guidelines for alcohol consumption and stress management pamphlets) or the control condition (*n* = 172, four phone check-ins < 5 min, guidelines for alcohol consumption and stress management pamphlets). Telephone follow-up assessments will occur at 4–6 weeks, 3 months, 6 months and 12 months post-baseline. The primary outcome is the Alcohol Use Disorders Identification Test (AUDIT) score administered at 3 months post-baseline. Secondary outcomes include change in AUDIT score (6 and 12 months post-baseline), change in number of past-month heavy drinking days, psychological distress, health and wellbeing, quality of life, client treatment evaluation and cost effectiveness.

**Discussion:**

This study will be one of the first RCTs conducted internationally to examine the impact of a standalone, structured telephone-delivered intervention to address problem alcohol use and associated psychological morbidity. The proposed intervention is expected to contribute to the health and wellbeing of individuals who are otherwise unlikely to seek treatment through mainstream service models, to reduce the burden on specialist services and primary care providers and to provide an accessible and proportionate response, with resulting cost savings for the health system and broader community.

**Trial registration:**

Australian New Zealand Clinical Trials Registry, ACTRN12618000828224. Pre-registered on 16 May 2018.

**Electronic supplementary material:**

The online version of this article (10.1186/s13063-019-3462-9) contains supplementary material, which is available to authorized users.

## Background

Alcohol consumption is the second leading cause of preventable morbidity and mortality in Australia, contributing to more than 100,000 hospitalisations and 3000 deaths each year [1] and increasing the risk for more than 60 different diseases and conditions [2]. Almost 50% of Australians are adversely affected by someone else’s drinking, costing those around them more than AUD$13 billion in out-of-pocket expenses and a reduced quality of life estimated at more than AUD$6 billion per annum [3]. Of the 20% of Australians meeting lifetime criteria for alcohol misuse (i.e. abuse or dependence), only one in five (22.4%) seeks help [4]. Co-occurring mental health issues, particularly anxiety and mood disorders, are also high [5]. While publicly funded treatment services are available in each state and territory, they have necessarily evolved to address the complex needs of the comparatively small minority of dependent drinkers falling at the severe end of the continuum (i.e. those with significant physical and mental health comorbidity and marked social disadvantage), often requiring expensive multi-disciplinary and inter-sectoral care. However, it is the substantially larger population of problem drinkers without complex medical or psychosocial needs, who are unlikely to seek treatment, who cause the greatest cost to society due to their sheer number [6]. As such, it is imperative that the available treatment options are broadened to address the entire continuum of problem alcohol use and that known barriers to treatment accessibility are addressed [7].

There is a substantial body of evidence on the effectiveness of brief interventions delivered in primary care settings for non-treatment-seeking people with problem alcohol use [8]. Structured, less intensive interventions can be used within a stepped care model, where individuals commence work on reducing their drinking before engaging in longer, more intensive programs or treatments, if needed [8]. There is also growing evidence for the benefit of multi-session brief interventions that typically address motivation, are solution focused and provide skills training, goal setting and craving management strategies [9–11]. Multi-component interventions which include integrated, evidence-based approaches (e.g. cognitive behavioural therapy and motivational interviewing) have been proposed to have an additive effect in treating problem alcohol use [12] as well as addressing comorbid mental health problems [9, 10, 13].

Most studies examining the effectiveness of brief interventions for problem alcohol use have been conducted in general health settings, particularly primary care, where problem alcohol use has been identified through opportunistic screening [14, 15]. Despite the effectiveness of such interventions, problem alcohol use remains poorly detected and treated within most healthcare settings [16–18]. Delivery of opportunistic interventions within primary care is sporadic at best, with multiple barriers to implementation in these settings (such as time, cost and lack of knowledge about when and how to implement such interventions) [19].

Additional barriers to accessing treatment for problem alcohol use include service accessibility (e.g. wait lists, service operating hours and difficulty in attending sessions scheduled at regular times in fixed locations) [20], geographical barriers (e.g. location, restricted transport options and scarcity of services particularly in regional/rural areas), the experience of self-stigma and concerns about anonymity. To overcome these barriers, attention has increasingly turned towards designing interventions that utilise different, flexible and more accessible modes of service delivery. Telephone-based support, such as 24/7 alcohol and drug helplines, are ideally placed to overcome many of the barriers to accessing treatment for problem alcohol use. Alcohol and drug helplines are available in every Australian state and territory, and they collectively respond to more than 140,000 calls each year [21]. The 24-h availability of such support offers increased accessibility for individuals in regional areas, as well as those requiring child care, those in full-time employment or those who feel stigmatised or have a preference for anonymity. These helplines are often the first point of contact for individuals seeking help for problem alcohol use. However, these inbound services traditionally provide a one-off response to the caller’s immediate request for assistance, with a focus on crisis support, information provision and referral to face-to-face treatment [21, 22].

This study will be one of the first to use randomised controlled methods to examine the efficacy of standalone, multi-session interventions for problem alcohol use delivered via telephone, despite evidence for the effectiveness of telephone-delivered interventions for other substances (e.g. tobacco and cannabis use) [23, 24]. A recent review of studies, of any methodological design, that examined telemedicine interventions for the treatment of substance use disorders concluded that this approach holds potential for effectiveness in reducing substance use [25]. Despite a paucity of research in the alcohol field, there is evidence from non-randomised research that proactive telephone-delivered interventions (i.e. outbound telephone counselling) are likely to be effective for problem alcohol use [23, 26]. With increasing support for the effectiveness of telephone-delivered interventions for a range of substance use problems, and growing concerns related to the increasing harms and costs associated with problem alcohol use across Australian communities, we will examine the impact of a multi-session, structured telephone-delivered intervention (Ready2Change, R2C [27]) to address problem alcohol use (and associated psychological morbidity) in a randomised controlled trial (RCT).

### Choice of comparator

Evidence from primary care settings (and some evidence from other healthcare settings) suggests that screening and a single occurrence of brief health education advice — either verbally or through the provision of self-help materials — yields short-term improvements in individuals’ alcohol consumption [15, 28, 29]. Data from several studies suggest that mere exposure to baseline questions about alcohol use can impact positively on alcohol consumption levels [30]. Baseline questioning effects may operate through similar mechanisms, prompting reflection and the self-regulation of behaviour [31]. Still, pooling effect sizes over large numbers of alcohol BI studies have been able to provide a powerful estimate of how this form of health promotion performs [15, 30, 32].

Therefore, to control for the effects of alcohol use assessment and frequency of contact, participants in the control group will receive brief check-in calls and be provided with health information pamphlets (see Additional file 2: Alcohol consumption pamphlet and Additional file 3: Stress management pamphlet). While participants in the control condition may experience some benefit from participation, we expect it will be less than that obtained for the active condition.

### Objectives

The aim of the study is to examine the efficacy of the R2C telephone-delivered structured intervention in reducing alcohol problem severity and related psychological distress in individuals with problem alcohol use (defined here as an Alcohol Use Disorders Identification Test (AUDIT) score of > 6 for females and > 7 for males) [33], compared with the provision of basic health information and weekly check-in calls (see Fig. 1).

**Fig. 1 Fig1:**
[figure not shown]
Primary and secondary outcomes [34–41]

### Trial outcomes

Primary and secondary outcomes for this trial are detailed in Fig. 1.

## Methods

### Design

This study is a single site, parallel group, two-arm superiority RCT, with participants randomly allocated to receive either the R2C intervention or the control condition (Fig. 2). The protocol follows Standard Protocol Items: Recommendations for Interventional Trials (SPIRIT) guidelines (see Table 1: SPIRIT figure and Additional file 1: SPIRIT checklist).

**Fig. 2 Fig2:**
[figure not shown]
Study design

**Table 1 Tab1:** SPIRIT table

			Intervention		Follow-up				
	Screening	Baseline	R2C	Control	4-6 week	3 month	Feed-back	6 month	12 month
Contacted by	R1	R1	Counsellor	R1	R2	R2	R1	R2	R2
Week	0	0	1-6	1-4	4-6	-	~13	-	-
Eligibility screen	X								
AUDIT	X					X		X	X
SADQ-C	X								
SIDAS	X								
Informed consent	X								
Allocation		X							
TLFB		X			X	X		X	X
Substance use		X				X		X	X
K10		X				X		X	X
EUROHIS-QOL 8-item index		X				X		X	X
Adverse events		X	X	X	X	X	X	X	X
Barriers to help-seeking		X							
Additional treatment enquiry					X	X		X	X
AQoL-6D		X				X		X	X
WHO HPQ		X				X		X	X
Cost data		X				X		X	X
Counselling sessions			X						
Self-help resources			X						
Information pamphlets			X	X					
CEST							X		
Qualitative feedback							X		

*R1* Researcher 1, *R2* Researcher 2

### Setting

The study is being conducted at Turning Point, a national addiction treatment and research centre in Melbourne, Victoria. Turning Point provides a range of clinical specialist treatment services for people affected by alcohol and other drugs across Australia, including a 24-h telephone counselling, information and referral service.

### Participants

A total of 344 participants (172 participants per trial arm) will be randomly allocated to one of the two study conditions.

### Inclusion/exclusion criteria

The inclusion and exclusion criteria are described in Fig. 3.

**Fig. 3 Fig3:**
[figure not shown]
Participation criteria

### Recruitment and screening

All assessments will be conducted over the telephone, using protocols developed in our pilot studies and previous cohort work [42]. A research assistant (Researcher 1) will perform eligibility assessments and baseline data collection (see Table 2). A second research assistant (Researcher 2) will perform follow-up data collection. Participants, Researcher 2 and the study statistician will remain blind to participant allocation.

**Table 2 Tab2:** Trial measures

	Data collected	Method
Screening measures	Demographic information *Structured questions*	Standard demographic characteristics (e.g. age, gender, education level)
	Problem alcohol use *AUDIT*	Assessed by the Alcohol Use Disorders Identification Test (AUDIT) [33]. A score of > 6 for women and > 7 for men warrants inclusion in the study
	Severity of alcohol dependence *SADQ-C*	Assessed by the Severity of Alcohol Dependence Questionnaire (SADQ-C) [54]. A score of 31 or higher indicates “severe alcohol dependence” and warrants exclusion from the study
	Presence/severity of suicidal thoughts *SIDAS*	Assessed by the Suicidal Ideation Attributes Scale (SIDAS) [55]. A score of 21+ indicates high risk of suicidal behaviour and warrants exclusion from the study
	Other inclusion/exclusion *Structured questions*	Structured questions querying self-reported information pertaining to the study’s inclusion/exclusion criteria (e.g. history of psychosis)
Outcome measures		
Primary outcome	Alcohol problem severity *AUDIT*	The primary outcome is alcohol problem severity at 3 months, assessed by the AUDIT. The time frame has been adapted to cover month prior to assessment (rather than year), so that planned follow-up assessments at 3, 6 and 12 months can be performed. Five short items from the recent Australian Institute of Health and Welfare (AIHW) National Drug Strategy Household Survey have been included to provide additional information on self-reported change in alcohol use and alcohol literacy
Secondary outcomes	Alcohol use patterns *TLFB*	Past-month (30 days) alcohol consumption and heavy drinking days, assessed by the Alcohol Timeline Follow-back (TLFB) [35]. Heavy drinking days are measured as > 40/60 g of alcohol (4/6 standard drinks)
	Substance use *AOD Self-Completion Form*	Assessed using items from the Victorian Department of Health and Human Services (DHHS) Victorian AOD Self-Completion Form [56], recording recent use of other drugs and frequency of use in the past 28 days
	Psychological distress *K10*	Assessed by the Kessler Psychological Distress Scale (K10) [36]
	Quality of life *EUROHIS-QOL 8-item index* *AQoL-6D*	Assessed by the EUROHIS-QOL 8-item index [37, 57] and Assessment of Quality of Life (AQoL-6D) [38]
	Cost effectiveness *AQoL-6D* *WHO HPQ* *Health-care* *Resource Use* *Questionnaire*	The incremental cost of treatment will be compared to the incremental benefits of treatment in terms of the primary outcomes and the difference in quality-adjusted life years (QALYs; assessed by the AQoL-6D). Work performance and productivity will be assessed by items from the WHO Health and Work Performance Questionnaire short form (WHO HPQ) [40]. Healthcare resource use is assessed using items from the 3Mg trial’s Health-care Resource Use Questionnaire [41]
	Adverse events *Structured questions*	During baseline, scheduled intervention/control calls, and follow-up calls, participants will be asked general questions: *“Have you had any health concerns recently* (baseline)/*since the last time you had telephone contact for this study?”*, *“Have you felt unwell or different since the last time you had telephone contact for this study?”* and *“Do you have any specific worries or complaints about your health in general?”*, as well as more specific questions: *“Has your alcohol use changed?”* and *“Has your mood changed?”*
Additional measures/participant feedback	Barriers to help-seeking *Structured questions*	Perceived barriers to treatment-seeking for alcohol problems will be identified through an open-ended question (*“What are the reasons that you have not sought treatment for your alcohol use in the past?”*) and from a list of 15 barriers (e.g. financial, stigma, readiness for change) developed by Schuler et al. [58]
	Treatment participation and satisfaction *CEST TCU ENG*	Assessed by the Client Evaluation of Self and Treatment (CEST) short form (TCU ENG) [39] (approximately 20% of the R2C intervention group)
	Qualitative feedback *Structured questions*	Questions asked will include: *“Which parts, if any, of the telephone intervention sessions were most helpful to you? How were these most helpful?”* and *“What did you think about the delivery, format and duration of the telephone intervention sessions?”* (approximately 20% of the R2C intervention group)
	Additional treatment enquiry *Structured questions*	Engagement in any additional treatment (e.g. inpatient/outpatient treatment) or mutual aid group attendance (AA, SMART Recovery) will be queried and recorded for all participants (exclusion criterion at screening only)

To recruit our target sample size, recruitment methods will be broad. Participants will be recruited from across Australia via a number of channels, including print, radio and online advertising (including social media), clinician referrals, helpline service referrals (i.e. interstate Alcohol and Drug Information Services that do not currently offer R2C-type outbound interventions) and opportunistic study promotion. Online advertising will be the primary recruitment strategy due to its broad reach and cost effectiveness [43]. In the case of online advertising, individuals will be linked to a secure Qualtrics form in which to enter their contact details. Individuals who express interest in participating will be called by Researcher 1 and verbally provided with detailed information about the study before being assessed for eligibility to participate. Those who are eligible will be provided with the Participant Information and Consent Form (PICF) and asked to provide verbal consent to participate by Researcher 1. Baseline data collection can be undertaken during this phone call or scheduled for a different time as preferred by the participant. Participants will be randomised on completion of the baseline assessment.

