The repeated measurements of the outcome variables will be analysed by fitting linear mixed models, with fixed effects for treatment and time, and their interaction, and random effects for subjects and assessments within subjects, using restricted maximum likelihood (REML). As well as accommodating missing values under the missing at random assumption, this method will allow the most suitable variance-covariance model for the repeated measures to be selected, using Akaike’s information criterion [63], and commonality of nonlinear trends over time to be explored via splines. The *F* test will be used to test for an overall group-by-time interaction, and the primary comparison, between groups, of their changes from baseline to 3 months follow-up will be based on a *t* test of the corresponding interaction contrast — this *t* test will utilise the predicted means and their variance-covariance matrix that are recovered from the fitted mixed model. Diagnostic plots of residuals will be assessed and, if deemed necessary, variance-stabilising transformations, such as the empirical logistic transformation, will be applied to the outcome variables and inferences will be based on the analyses conducted on the transformed scale. In a series of exploratory analyses, mixed models with covariates for gender, illicit drug use, extent of exposure to the intervention, exposure to other treatments or programs, level of psychological distress and, as appropriate, level of alcohol use at baseline will be fitted, including their interactions with treatment group, in order to identify moderating factors. A sensitivity analysis, to assess the impact of missing 3-month data on the primary outcome, will use a “tipping point” approach [63]. Categorical, ordinal and binary outcomes will be analysed in a similar way using generalised linear mixed models (GLMMs). The complete list of candidate covariates and details of the analyses will be specified in a statistical analysis plan that will be reviewed and approved by the Principal Investigator prior to database lock. Analyses will be conducted using the most appropriate procedures in GenStat, R and STATA.

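### The primary test subtracts an eligibility-screen AUDIT whose recall period is not stated; comparing 3-month AUDIT scores with the screen as covariate is safer and more powerful

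*Protocol article*

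**What the plan says.** The primary outcome row of Table 2 (Recruitment and screening) reads: "The primary outcome is alcohol problem severity at 3 months, assessed by the AUDIT". The Statistical analysis plan section tests "the primary comparison, between groups, of their changes from baseline to 3 months follow-up" as an interaction contrast in a linear mixed model, and Sample size estimation powers the same contrast.

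Table 1 marks AUDIT at Screening and at 3, 6 and 12 months, with no mark under Baseline. The other repeated outcomes in that table (TLFB, substance use, K10, EUROHIS-QOL, AQoL-6D, WHO HPQ, cost data) are all marked under Baseline.

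Table 2 lists AUDIT twice. The screening row gives the entry rule, "A score of > 6 for women and > 7 for men warrants inclusion in the study", and no recall period. The outcome row says "The time frame has been adapted to cover month prior to assessment (rather than year", and gives as the reason "so that planned follow-up assessments at 3, 6 and 12 months can be performed".

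On timing, "Baseline data collection can be undertaken during this phone call or scheduled for a different time as preferred by the participant", and "Participants will be randomised on completion of the baseline assessment". Table 1 puts both Screening and Baseline at week 0.

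**The concern.** The time-zero value in the primary change can only be the score that admitted the participant. Two things follow.

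First, that score is cut off from below by the entry rule, so part of any later fall is regression to the mean.

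Second, the article does not say whether it covers a month or a year. The text reads as if only the follow-up instrument was shortened. If so, the change subtracts scores that measure different periods. Frequencies and harms counted over twelve months tend to be higher than those counted over one, even if drinking is unchanged.

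Two things are at stake: how the fall in each arm is read against the planned improvements of 8 and 4 points, and the precision of the primary test. A change contrast gives the baseline score a fixed weight of one. If that score correlates weakly with the 3-month score, subtracting it adds more noise than it removes.

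**Working it through.** **Inputs** (Sample size estimation): between-subject variance 23.8; within-subject variance 49.8; 120 evaluable per arm; reductions of 8 and 4, so a difference of 4; two-sided 5% test; equicorrelation within subjects. Total variance = 23.8 + 49.8 = 73.6. ICC = 23.8/73.6 = 0.323, as stated.

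**The plan's own figure.** Variance of a change = 2 × 49.8 = 99.6. SE of the contrast = √(99.6 × 2/120) = 1.288. Non-centrality = 4/1.288 = 3.105. Power from the non-central t with 238 df is 87.1% (normal approximation 87.4%), against 85% stated. The stated value is slightly conservative, and nothing here turns on the gap. The F test for the sustained effect gives 90.5% against 90% stated, and 120/0.70 rounds up to the stated 172.

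**Change contrast against 3-month score with covariate.** Let r be the correlation between screening and 3-month AUDIT, with both variances held at 73.6.

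- Change: variance = 2 × 73.6 × (1 − r).
- 3-month score adjusted for the screen: variance = 73.6 × (1 − r²).
- SE = √(variance × 2/120). Power is from the non-central t for a difference of 4, with 238 df for change and 237 with the covariate.

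| r | Change: variance | SE | Power | Covariate: variance | SE | Power |
|---|---|---|---|---|---|---|
| 0.323 (plan) | 99.6 | 1.288 | 87% | 65.9 | 1.048 | 97% |
| 0.2 (assumed) | 117.8 | 1.401 | 81% | 70.7 | 1.085 | 96% |
| 0.1 (assumed) | 132.5 | 1.486 | 76% | 72.9 | 1.102 | 95% |
| 0 (assumed) | 147.2 | 1.566 | 72% | 73.6 | 1.108 | 95% |

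The 3-month score with no covariate has variance 73.6 whatever r is, and so 95% power. Below r = 0.5 the change contrast does worse than ignoring the screen altogether, since 2(1 − r) > 1. The plan's own 0.323 is already below that point.

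**Is the treatment effect biased?** A simulation used the plan's variances, 120 per arm, a true control fall of 4 and a true difference of −4. It assumed a mean of 15 or 20, a screening score raised by 0, 3 or 5 points for longer recall, and entry either unrestricted or limited to scores above 7 (2,000 runs per setting).

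- The between-arm estimate stayed between −3.96 and −4.03.
- Rejection under no effect was 4.2% to 5.6%.
- The control arm's apparent change ran from −4.0 to −9.8. With no recall shift, the entry cut alone moved it to −4.8 (mean 20) or −5.8 (mean 15).

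Scores were drawn as normal, without the bounds of the scale.

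**The case against.** The strongest reply is that no sentence says the screening AUDIT covered a year. The adaptation is described for the outcome instrument, whose baseline value belongs to the primary contrast, and the follow-up schedule is the reason for adapting it, not necessarily a limit on where the adapted form is used. The figures with the outcomes and participation criteria are not shown, nor is the full protocol. This stands: a reader might infer that the baseline is a past-year score, but the article leaves that open.

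A reader might also infer that the estimated treatment effect is biased. It is not. The score is taken before randomisation, and shift and selection cancel between arms. Nor can a size be put on a recall artefact, because the article offers no figure for one. A common shift would not alter the 4-point difference on which power rests.

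A reader might take the freedom to schedule the baseline call later as separating the screen from randomisation by an open interval. Table 1 places both at week 0, so that is not supported.

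Two further replies carry less weight. The pilot variance of 49.8 may already contain recall noise; the article does not say, and if it does, the 87% row applies. Choosing the covariance model by Akaike's criterion helps to give an honest standard error. With separate arm means at time zero and complete data, however, the estimate is still the difference in mean change, so the lost precision is not recovered.

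**Conclusion.** The point holds as one of interpretation and precision. The baseline of the primary contrast is the selection score, and its recall period is not fixed in the article. Within-arm falls from it mix treatment response, regression to the mean and possibly a change of recall, so they should not be set against the planned 8 and 4.

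For the primary test, the change contrast costs about 10 percentage points of power at the plan's own variances (87% against 97%), whatever the recall period. If a mismatch weakens the correlation, the gap widens to about 23 points at r = 0 (72% against 95%). These figures assume equal variances at the two times, 120 evaluable per arm and a 4-point difference. The correlations below 0.323 are assumptions.

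**What to change.** Before database lock and unblinding:

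1. Do not model the screening AUDIT as a time-zero response. Define the primary comparison as the between-arm difference in past-month AUDIT at 3 months, from the mixed model of the 3-, 6- and 12-month scores, with screening AUDIT and gender (the randomisation stratum) as covariates. The article's Cost effectiveness section already adjusts for baseline outcome and gender.
2. Do not report falls from screening within an arm as improvement.
3. State the recall period of the screening AUDIT.
4. Optionally, add a past-month AUDIT to the baseline call, before the envelope is opened, for those still to be recruited. Trial status reports 285 of 344 randomised, so this can reach at most 59 (17%) and cannot be the main remedy.

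The cost is a rewording of the primary contrast before unblinding and a little more analysis work. Participants with no AUDIT after randomisation leave the model, but in the planned model they would inform the time-zero means and say almost nothing about 3 months. The planned tipping-point analysis still addresses missing 3-month data.
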